## Abstract

**Background:**

Thoracic epidural analgesia is the standard postoperative pain management strategy in esophageal cancer surgery. However, paravertebral block analgesia may achieve comparable pain control while inducing less side effects, which may be beneficial for postoperative recovery. This study primarily aims to compare the postoperative quality of recovery between paravertebral catheter versus thoracic epidural analgesia in patients undergoing minimally invasive esophagectomy.

**Methods:**

This study represents a randomized controlled superiority trial. A total of 192 patients will be randomized in 4 Dutch high-volume centers for esophageal cancer surgery. Patients are eligible for inclusion if they are at least 18 years old, able to provide written informed consent and complete questionnaires in Dutch, scheduled to undergo minimally invasive esophagectomy with two-field lymphadenectomy and an intrathoracic anastomosis, and have no contra-indications to either epidural or paravertebral analgesia. The primary outcome is the quality of postoperative recovery, as measured by the Quality of Recovery-40 (QoR-40) questionnaire on the morning of postoperative day 3. Secondary outcomes include the QoR-40 questionnaire score Area Under the Curve on postoperative days 1–3, the integrated pain and systemic opioid score and patient satisfaction and pain experience according to the International Pain Outcomes (IPO) questionnaire, and cost-effectiveness. Furthermore, the groups will be compared regarding the need for additional rescue medication on postoperative days 0–3, technical failure of the pain treatment, duration of anesthesia, duration of surgery, total postoperative fluid administration day 0–3, postoperative vasopressor and inotrope use, length of urinary catheter use, length of hospital stay, postoperative complications, chronic pain at six months after surgery, and other adverse effects.

**Discussion:**

In this study, it is hypothesized that paravertebral analgesia achieves comparable pain control while causing less side-effects such as hypotension when compared to epidural analgesia, leading to shorter postoperative length of stay on a monitored ward and superior quality of recovery. If this hypothesis is confirmed, the results of this study can be used to update the relevant guidelines on postoperative pain management for patients undergoing minimally invasive esophagectomy.

**Trial registration:**

Netherlands Trial Registry, NL8037. Registered 19 September 2019.

## Background

Esophageal cancer is the 9th most common cancer worldwide and is increasingly diagnosed in the Western world, mainly due to the growing incidence of adenocarcinoma [1]. Esophagectomy is the core of curative treatment for esophageal cancer, achieving a 5-year survival rate of 40–50% when preceded by neoadjuvant therapy [2, 3]. Traditional open transthoracic esophagectomy is associated with substantial postoperative thoracic pain, mainly due to the large intercostal incision, which may lead to decreased mobility, (pulmonary) complications, and delayed recovery [4]. In this light, adequate pain management is essential during the early postoperative phase. Thoracic epidural analgesia is the current gold standard for pain control in this context, as it was shown to be superior to systemic opioids in terms of pain control and pulmonary complications after open esophagectomy [5, 6]. However, over the last decades, minimally invasive esophagectomy (MIE) is increasingly adopted, which is associated with less postoperative pain when compared to open surgery [7–9]. Furthermore, enhanced recovery protocols have been introduced for esophagectomy, aiming at fast mobilization and recovery after MIE [10–12]. As potential adverse effects of epidural analgesia include failed catheter placement, postoperative hypotension, and diminished mobilization, epidural analgesia may be counterproductive in achieving some of the key aims of enhanced recovery protocols for MIE [13, 14]. Moreover, epidural analgesia is associated with severe neurological complications such as epidural hematoma or abscess formation in up to 1 in 1000 patients, which should be considered a serious issue [15, 16]. Therefore, the value of epidural analgesia for MIE needs to be reconsidered in a state-of-the-art treatment setting.

In previous systematic reviews that included patients undergoing a variety of thoracotomy or thoracoscopy procedures (mostly lung surgery), paravertebral analgesia was found to achieve comparable pain relief while inducing less postoperative hypotension, urinary retention, and nausea when compared to epidural analgesia [17, 18]. While these results seem to represent rather solid evidence in favour of paravertebral analgesia for thoracic surgery in general, transthoracic esophagectomy includes an abdominal phase in addition to the thoracic procedure. This means that results from studies that primarily included patients undergoing only thoracic surgery may not be generalizable to the setting of transthoracic esophagectomy. The hypothesized advantages of paravertebral analgesia over epidural analgesia were previously explored in systematic reviews of patients undergoing esophagectomy, which revealed that paravertebral analgesia achieves comparable pain control and possibly causes less hypotensive events [19, 20]. However, both reviews highlighted the lack of high-quality prospective studies in patients undergoing MIE [19, 20].

Most available studies on the efficacy of paravertebral analgesia after esophagectomy are retrospective in nature and included patients who underwent resection by an open approach, implying a substantial risk of bias and the possibility that these results cannot be generalized to the setting of MIE. Therefore, the primary aim of the current study is to compare the postoperative quality of recovery between paravertebral and epidural analgesia in patients undergoing MIE. Secondary objectives are to compare the efficacy, side-effects, and cost-effectiveness between these analgesic modalities. The hypothesis of this study is that paravertebral analgesia achieves comparable pain control while causing less side-effects, leading to shorter length of stay on a monitored ward and superior postoperative quality of recovery compared to epidural analgesia.

## Methods

### Design

This study represents a multicenter randomized superiority controlled trial that is conducted in 4 Dutch high-volume centers for esophageal cancer surgery: (1) University Medical Center Utrecht, (2) Amsterdam UMC (3), Catharina Hospital Eindhoven, and (4) Hospital Group Twente Almelo. The current version of the study protocol (V1.2) was approved by the Medical Ethical Committee of the University Medical Center Utrecht (reference number 19–588) and was prospectively registered in the Netherlands Trial Registry (trial number NL8037). Amendments to the protocol will first be presented to the ethics board and the approved adjustments are then also processed in the Netherlands Trial Registry. As this study is considered to carry negligible risks for participating patients, a data monitoring committee (DMC) was judged to be redundant.

### Patient population

Patients who are scheduled to undergo elective minimally invasive esophagectomy with two-field lymphadenectomy, gastric conduit reconstruction, and intrathoracic anastomosis (i.e. Ivor Lewis procedure) are eligible for participation and will be included according to the flowchart in Fig. 1. Exclusion criteria are severe comorbidity (ASA score > III), coagulation disorders that prohibit epidural analgesia according to the Dutch Society for Anesthesiology guidelines “Neuraxisblock and anti-coagulation”, other contraindications for epidural analgesia (e.g. local skin infection), allergy to local anesthetics, chronic opioid use prior to esophagectomy (> 3 months prior to the day of surgery), renal failure (eGFR < 50 mL/min.), inability to provide informed consent or complete questionnaires in Dutch, cervical lymph node dissection, and pregnancy.

**Fig. 1 Fig1:**
[figure not shown]
PEPMEN inclusion flowchart

### Allocation to the treatment arms

The coordinating investigators and involved trial nurses will screen patients for eligibility and obtain informed consent during patients’ visits to the preoperative outpatient clinic. After inclusion and ultimately the day before surgery, one of the coordinating investigators or trial nurses will enter the patient in Castor EDC, which is the primary data capturing platform for this study and allows digital randomization. Randomization will be performed in a 1:1 ratio and stratified per including center to minimize the risk of center bias. The coordinating investigators of the study will ensure that patients receive the allocated analgesic modality at the time of esophagectomy. As a sham epidural catheterization would need to be performed prior to the induction of general anesthesia in the paravertebral group, which is considered unethical, patients will not be blinded. Health care providers will also not be blinded, since blinding would likely increase the risk of errors in pain management to an unacceptable extent.

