### Paravertebral analgesia (intervention)

At the start of the thoracic phase of MIE, the surgeon places a paravertebral catheter at level T4–5 under thoracoscopic vision. After administering an initial bolus of 20 mL of bupivacaine 0.125%, continuous infusion of bupivacaine 0.125% is started and postoperatively continued at an infusion rate of 8–12 mL/hour, depending on the patient’s weight and comfort. Patient-controlled intravenous opioid analgesia is additionally provided according to the local protocol in each center.

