### Statistical analyses

The difference in primary outcome between the two groups will be compared using an independent t-test based on the intention-to-treat principle. The primary outcome will be analyzed with a general linear model for continuous outcomes. In the analysis, the preoperative (baseline) QoR-40 measurement, age, and comorbidities will be included as potential confounders. Validity of the model (normality, homoscedasticity) will be assessed by means of residue analysis. A per-protocol analysis will additionally be performed in the same manner. Analyses of the secondary outcomes are performed depending on data type and distribution. Chi-square tests will be performed for categorical data. The t-test or Mann-Whitney U test will be used to compare continuous outcomes with a normal or non-normal distribution, respectively.

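### Randomisation is stratified by centre but neither stated analysis of the primary outcome includes centre; if centre predicts QoR-40, the t-test is conservative and less powerful than a centre-adjusted analysis

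*Protocol article*

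**What the plan says.** On the design, Allocation to the treatment arms states: "Randomization will be performed in a 1:1 ratio and stratified per including center to minimize the risk of center bias". The Abstract gives the number of strata: "A total of 192 patients will be randomized in 4 Dutch high-volume centers for esophageal cancer surgery".

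On the analysis, the Statistical analyses section makes two statements about the same outcome. The first is: "The difference in primary outcome between the two groups will be compared using an independent t-test based on the intention-to-treat principle". The second is: "The primary outcome will be analyzed with a general linear model for continuous outcomes". The model's covariates follow: "In the analysis, the preoperative (baseline) QoR-40 measurement, age, and comorbidities will be included as potential confounders". Centre is not on that list, and no other sentence in the article adds it. The per-protocol analysis is to be run in the same way, so it inherits the omission.

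On care that differs between centres, the section on paravertebral analgesia states: "Patient-controlled intravenous opioid analgesia is additionally provided according to the local protocol in each center". The section on epidural analgesia likewise leaves the intravenous opioid to local practice.

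**The concern.** Stratifying by centre, with near-equal arms in each, stops differences between centres from contributing to chance differences between arms. The treatment difference is then less variable than under simple randomisation. A t-test that ignores centre does not know this. It leaves between-centre variance in its standard error, so the interval is wider, and the actual alpha lower, than they should be. The gain in precision that stratification bought is left unused.

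The mismatch matters only if centre predicts QoR-40. That is plausible here: patient-controlled opioid follows each centre's own protocol, and the Discussion lists pain and comfort among the domains of the questionnaire. At stake are the precision of the primary estimate and the agreement between design and analysis, not the validity of the comparison.

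**Working it through.** **Inputs from the protocol article.** Sample size section: SD 14, difference 6, power 80%, alpha 0.05, 86 per arm (172), 10% loss, 192 in total. Allocation section: 1:1, stratified by centre. Abstract: four centres. Sidedness is not stated; two-sided reproduces the stated number, whereas one-sided would give 68 per arm.

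**Assumptions, not in the documents.** SD 14 is the total SD over all centres. A share c of that variance lies between centres, with c = 0, 0.05, 0.10 or 0.20. Arms are near-balanced within each centre.

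**Step 1: reproduce the plan.** n per arm = 2 × (1.960 + 0.842)² × 14² / 6² = 85.5, rounded up to 86, or 172 in total. 172 / 0.90 = 191.1, rounded up to 192. Power at 86 per arm is 80.2% by the normal approximation (79.8% by the noncentral t). The plan's figures reproduce.

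**Step 2: two standard errors.** The t-test reports SE_rep = 14 × √(2/86) = 2.135. Under stratified allocation the true value is SE_true = 14 × √(1 − c) × √(2/86). Their ratio is 1/√(1 − c).

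**Step 3: operating characteristics.**
- Actual alpha of the t-test = 2 × [1 − Φ(1.96 × SE_rep / SE_true)]
- Power of the t-test = Φ[(6 − 1.96 × SE_rep) / SE_true]
- Power with centre adjusted = Φ[6 / SE_true − 1.96]

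Worked for c = 0.10: SE_true = 2.135 × √0.90 = 2.025 and the ratio is 1.054. Alpha = 2 × [1 − Φ(2.066)] = 3.9%. Unadjusted power = Φ[(6 − 4.185) / 2.025] = Φ(0.896) = 81.5%. Adjusted power = Φ(2.963 − 1.960) = Φ(1.003) = 84.2%.

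| Centre share c | SE_true | Interval too wide by | Alpha, t-test | Power, t-test | Power, centre adjusted |
|---|---|---|---|---|---|
| 0% | 2.135 | 0% | 5.0% | 80.2% | 80.2% |
| 5% | 2.081 | 2.6% | 4.4% | 80.9% | 82.2% |
| 10% | 2.025 | 5.4% | 3.9% | 81.5% | 84.2% |
| 20% | 1.910 | 11.8% | 2.8% | 82.9% | 88.1% |

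**Step 4: check by simulation.** With four centres, 172 patients, permuted blocks of four (an assumption) and 20,000 trials per scenario, c = 0.10 gave a type I error of 3.7% for the t-test and 4.9% with centre in the model. Power was 81.2% and 84.0%. This agrees with the formulas.

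All these figures compare a t-test without covariates with the same comparison adjusted for centre alone. They do not describe the linear model with baseline QoR-40, age and comorbidities.

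**The case against.** The strongest reply is that no stated operating characteristic fails. The documents give no between-centre variance for QoR-40. At zero nothing is lost, up to a 10% share the loss is under three points of power, and nothing in the documents supports a share as high as 20%. The setting is fairly uniform: high-volume Dutch centres, one operation and common eligibility. The Discussion's remark that centres may change other perioperative care concerns change over time, which a fixed centre effect captures only in part. All of this stands, and it is why the loss is put conditionally.

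Two technical replies also stand. The formulas need near-equal arms within centres, and the article states stratification and the ratio but no blocking. In the linear model, the listed covariates may absorb part of any centre difference, so its loss may be smaller.

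It can also be said that a journal article condenses, that strata are often left to the analysis plan, and that a list of possible confounders need not be complete, since a factor balanced by design is not a confounder. This carries less weight. The article is not silent on adjustment: it names its covariates, and the only stratification factor is not among them. An analysis plan that added centre would depart from the published model.

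A reader might infer that the omission biases the treatment effect, inflates type I error or leaves the trial underpowered. The documents do not support any of these. The error is conservative, and with a total SD of 14 the t-test keeps at least the 80.2% power of the normal-approximation calculation. Nor do they support stating a loss of power as established fact.

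**Conclusion.** The mismatch between design and analysis is certain; its consequence is conditional. If centre explains 5% to 20% of the variance in QoR-40, the t-test's actual alpha is 4.4% to 2.8%, and it gives up 1.3 to 5.2 points of power against a centre-adjusted analysis (82.2 − 80.9 and 88.1 − 82.9). This rests on near-balance within centres, a total SD of 14 and 86 evaluable patients per arm, and it applies directly only to the t-test. What is lost is power above the planned level. The point is therefore a recommended improvement in efficiency and coherence, not a threat to validity. It is worth making because the trial is sized close to 80% and the remedy needs no new data.

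**What to change.** In Statistical analyses, name the general linear model as the single primary analysis and add centre to its covariates as a fixed effect with four levels. Do the same in the per-protocol analysis. Report the unadjusted t-test only as supportive, because adding centre to the model alone would leave an analysis that ignores the strata with equal standing. No change to secondary regression models is asked for, as the article names none. Settle this before the data are analysed, so that it cannot look like a choice made on the results.

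Cost: three degrees of freedom out of about 170, and a short text change. The sample size does not change.

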### Surgical technique

All patients will undergo MIE with two-field lymphadenectomy, gastric conduit reconstruction, and an intrathoracic anastomosis. The operation may be performed by conventional or robot-assisted thoracolaparoscopic surgery. The procedure starts with an abdominal laparoscopic phase, which involves mobilization of the stomach, abdominal lymphadenectomy and gastric conduit construction. Then, the patient will be placed in (semi) prone position for thoracoscopy to mobilize the esophagus and perform a mediastinal lymphadenectomy. One of the trocar ports is widened to a mini-thoracotomy for specimen extraction and when indicated, for the creation of the anastomosis. Gastrointestinal continuity is finally restored by a stapled or hand-sewn intrathoracic esophagogastric anastomosis. A maximum of one thoracic drain is placed on each side.

### Paravertebral analgesia (intervention)

At the start of the thoracic phase of MIE, the surgeon places a paravertebral catheter at level T4–5 under thoracoscopic vision. After administering an initial bolus of 20 mL of bupivacaine 0.125%, continuous infusion of bupivacaine 0.125% is started and postoperatively continued at an infusion rate of 8–12 mL/hour, depending on the patient’s weight and comfort. Patient-controlled intravenous opioid analgesia is additionally provided according to the local protocol in each center.

### Epidural analgesia (control)

An epidural catheter is placed by the anesthesiologist at an intervertebral level between T5 and T8 prior to the induction of general anesthesia. After induction, a bolus of 5–10 mL of bupivacaine 0.25% is administered and traditional continuous epidural analgesia is initiated (bupivacaine 0.125% + sufentanil 0.5 mcg/ml) in a dose of 6–14 mL/hour, depending on the patient’s weight and comfort. Patient-controlled intravenous opioid analgesia is provided as escape medication according to the local protocol in each center.

### Outcome measures

The primary outcome measure is the total score on the Quality of Recovery 40 (QoR-40 [21]) questionnaire on the morning of postoperative day 3. The QoR-40 is a validated composite endpoint that can be used to evaluate analgesic modalities for postoperative pain control [22]. The main secondary outcome measures include the QoR-40 scores on postoperative days 1–2, the patient’s perception of postoperative pain management on days 1–3 (International Pain Outcomes (IPO) questionnaire), the need for escape pain medication on days 1–3, additional opioid consumption on days 1–3, technical complications, analgesia related side-effects, need for inotropic and vasopressive medication, length of stay on a monitored unit and in the hospital, postoperative complications, quality of life at 3 and 6 months after surgery, pain at 3 and 6 months after surgery (VAS score), and cost-effectiveness.

### Data collection

All data will be collected and stored in Castor EDC (https://www.castoredc.com) and the coordinating investigators will oversee the overall data collection process. Castor EDC generates a subject number for each patient and securely stores all entered research data in a pseudonymized fashion. A code file that links subjects numbers to individual patients will be securely stored in each center, and will only be accessible to authorized study staff. Collected baseline data (age, gender, body mass index, comorbidities), treatment details (neoadjuvant therapy, surgical techniques, postoperative complications, mortality), and data regarding blood pressure (i.e. vasopressor and inotropic use, fluid administration, weight) will be prospectively entered in a case report form with built-in validation checks. Patient-reported outcome measures (PROMs) will be collected during the postoperative hospitalization by asking patients to complete the QoR-40 and IPO questionnaires on postoperative days 1, 2, and 3. Furthermore, Quality of life questionnaires (EORTC QLQ-C30 and QLQ-OG25) will be sent to patients before surgery, at 3 months follow-up, and at 6 months follow-up after esophagectomy. Pain scores (VAS) at 3 and 6 months after esophagectomy will be collected and registered during the patients’ regular outpatient follow-up visits. The timeline of the study procedures is summarized in Fig. 2.

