### Sample size

The QoR-40 questionnaire was used as the primary outcome measure to calculate a sample size based on superiority of paravertebral analgesia when compared to epidural analgesia [21]. Backward and forward translations of the QoR-40 were validated by the study consortium to ensure the accuracy of the Dutch version. Based on previous literature, a QoR-40 score of 182 points with a standard deviation of 14 on postoperative day 3 is expected in the control group [23]. A difference of 6 points on the QoR-40 was assumed to indicate a minimally clinically relevant difference based on literature [24]. Hence, a total sample size of 172 patients is required (86 patients per group) to detect this difference with a statistical power of 80% and a significance level of (alpha) *P* < 0.05. Anticipating a 10% loss to follow up, 192 patients will be included. Only patients who withdraw before surgery will be replaced by new subjects.

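### Quality of life is measured before surgery, but the stated rule for continuous secondary outcomes gives that baseline no role, so the 3- and 6-month comparisons are valid but less precise than they could be

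*Protocol article*

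**What the plan says.** All places are in the protocol article, under Methods.

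- **Data collection:** "Quality of life questionnaires (EORTC QLQ-C30 and QLQ-OG25) will be sent to patients before surgery, at 3 months follow-up, and at 6 months follow-up". A pre-surgery score is therefore planned for both instruments.
- **Outcome measures:** the main secondary outcomes include "quality of life at 3 and 6 months after surgery".
- **Statistical analyses, secondary outcomes:** "Analyses of the secondary outcomes are performed depending on data type and distribution". For continuous data the rule is: "The t-test or Mann-Whitney U test will be used to compare continuous outcomes with a normal or non-normal distribution, respectively".
- **Statistical analyses, primary outcome:** in the general linear model, "the preoperative (baseline) QoR-40 measurement, age, and comorbidities will be included as potential confounders".
- **Allocation to the treatment arms:** randomisation is 1:1 and stratified by centre.

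No section assigns the pre-surgery quality-of-life score a part in the quality-of-life comparison.

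**The concern.** The trial asks patients to complete two questionnaires before surgery and then names a secondary analysis that, read as written, does not use the answers. Patients differ in quality of life before they are operated on, and some of that difference persists at 3 and 6 months. A two-sample test on the follow-up score leaves it in the error term, whereas a model with the pre-surgery score removes the part that baseline predicts. The authors already take this approach for the QoR-40, so the two parts of the same section treat similar data differently.

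What is at stake is the width of the confidence intervals for a main secondary outcome. The trial was sized on the QoR-40 alone, so there is no separate allowance of patients for quality of life.

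**Working it through.** **Inputs from the documents.** Under Sample size: control mean 182 and SD 14 ("a QoR-40 score of 182 points with a standard deviation of 14 on postoperative day 3 is expected in the control group"), a relevant difference of 6 points, 80% power, alpha 0.05, 86 per group, 172 in total, and 192 after 10% loss. No figure is given for quality of life.

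**Assumption.** The correlation r between pre-surgery and follow-up quality of life is not in the documents. It is varied from 0.2 to 0.7.

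**Step 1: reproduce the plan's own figure.** With two-sided alpha (sidedness is not stated, but two-sided reproduces the figure):

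n per group = 2 × (1.960 + 0.842)² × 14² / 6² = 85.5, rounded up to 86, so 172 in total. Then 172 / 0.90 = 191.1, rounded up to 192.

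Both figures agree with the protocol and are not in dispute.

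**Step 2: effect of baseline adjustment.** Compared with a t-test on the follow-up score, a linear model that includes baseline multiplies the variance of the treatment difference by 1 − r². The confidence interval width is multiplied by √(1 − r²). An unadjusted test needs 86 / (1 − r²) patients per group to match an adjusted analysis of 86 per group. The last column, 2(1 − r), is the variance factor for a t-test on change from baseline, assuming equal variances before and after surgery.

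| r | Variance factor 1 − r² | Variance cut (r²) | CI width factor | CI narrower by | Unadjusted n per group to match | Change-score factor 2(1 − r) |
|---|---|---|---|---|---|---|
| 0.2 | 0.96 | 4% | 0.980 | 2% | 89.6 | 1.6 |
| 0.3 | 0.91 | 9% | 0.954 | 5% | 94.5 | 1.4 |
| 0.4 | 0.84 | 16% | 0.917 | 8% | 102.4 | 1.2 |
| 0.5 | 0.75 | 25% | 0.866 | 13% | 114.7 | 1.0 |
| 0.6 | 0.64 | 36% | 0.800 | 20% | 134.4 | 0.8 |
| 0.7 | 0.51 | 49% | 0.714 | 29% | 168.6 | 0.6 |

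At r = 0.7, 0.51 is the share of the variance that remains, so the cut is 49%.

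**Step 3: what this means at the planned size.** With 86 per group, the standardised difference detectable with 80% power is (1.960 + 0.842) × √(2/86) = 0.427 SD without adjustment. At r = 0.5 it is 0.427 × 0.866 = 0.370 SD. For a difference of 6/14 = 0.43 SD, power would be about 80% unadjusted and about 90% adjusted at r = 0.5. This borrows the primary outcome's standardised effect for illustration only, and it assumes that 86 per group return the questionnaires. The percentages in the table do not depend on the sample size.

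**Step 4: would change scores do as well?** No. The gap between the two factors is 2(1 − r) − (1 − r²) = (1 − r)², which is never negative. At r = 0.5 a change score gains nothing over the plain follow-up score, and below 0.5 it is less precise.

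**The case against.** **The rule is generic.** The sentence on continuous outcomes covers a long, mixed list and does not name quality of life. It also does not rule out testing change from baseline. A reader might infer that the protocol commits to discarding the baseline, but the text does not go that far. This objection stands in part. No role for the baseline is stated, and change scores would be no better than adjustment.

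**Such detail belongs in the analysis plan.** This is a condensed article, and covariates for one secondary outcome are often fixed elsewhere. Had the article been silent, there would be no point to make. It does, however, name the tests and the rule for choosing between them, and it reserves baseline adjustment for the primary outcome. That is a stated method and open to comment.

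**Nothing is invalid.** This stands in full. A reader might infer that ignoring the baseline biases the result. Allocation is randomised, so the unadjusted comparison is unbiased, and its standard error already allows for chance imbalance.

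**The size is assumed.** This also stands. Major surgery and several months separate the measurements, so a low correlation cannot be excluded. At 0.2 to 0.3 the gain is only 4% to 9% in variance.

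**Wider claims lack figures.** A reader might infer further losses from leaving out centre, from testing the two visits separately, or from moving between a t-test and a rank test across visits. The documents provide nothing from which to size the first two. The third is possible under the rule, but no consequence is shown.

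**Conclusion.** The point holds as a matter of efficiency in a secondary outcome. The stated rule leaves the collected pre-surgery quality-of-life score unused, and the 3- and 6-month comparisons would then be valid but wider than necessary. The size depends on a correlation that the documents do not give: modest near 0.2, and substantial from about 0.5 upwards. It also rests on the usual linear-model approximation, with a common baseline slope in the two groups.

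The primary analysis and the sample size are not affected. The point should not be carried over to VAS pain at 3 and 6 months, because Data collection describes those scores only at follow-up visits.

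**What to change.** For each QLQ-C30 and QLQ-OG25 scale, replace the two-sample test with a linear model of the follow-up score on treatment group, pre-surgery score and centre. Either of two forms will serve:

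- a separate ANCOVA at 3 and at 6 months; or
- one mixed model for both visits with visit and group-by-visit terms, letting the covariate effects differ by visit. With complete data this makes essentially the same comparison at each visit.

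Either form captures the gain shown above, so the choice can follow the trial team's preference. Report the adjusted mean difference with its 95% confidence interval at each visit. Keep the Mann-Whitney U test as a sensitivity analysis, so that the main estimate is a mean difference on every scale and at both visits.

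The cost is a few sentences in the analysis plan, settled before outcome data are examined. No new questionnaires, visits or patients are needed, because the baseline questionnaire is already scheduled and centre is already recorded for stratification.

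### Late pain (VAS at 3 and 6 months) has no preoperative VAS named in the text and is to be compared by an unadjusted test, which costs precision and blurs the meaning of chronic pain

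*Protocol article*

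**What the plan says.** Outcome measures closes its list of main secondary outcomes with "pain at 3 and 6 months after surgery (VAS score), and cost-effectiveness". The abstract describes the late outcome as "chronic pain at six months after surgery".

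Data collection gives the method: "Pain scores (VAS) at 3 and 6 months after esophagectomy will be collected and registered during the patients’ regular outpatient follow-up visits". No other time point for the VAS appears in the text. The baseline list in the same section reads "Collected baseline data (age, gender, body mass index, comorbidities" and closes there, without a pain score. The two EORTC questionnaires (QLQ-C30 and QLQ-OG25), by contrast, "will be sent to patients before surgery, at 3 months follow-up, and at 6 months follow-up after esophagectomy", so patients already receive a questionnaire at a preoperative time point.

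Statistical analyses puts the preoperative QoR-40, age and comorbidities into the model for the primary outcome. For secondary outcomes it chooses the test by data type and distribution: for continuous ones, the t-test if normal and Mann-Whitney U if not. Neither uses a baseline value or center.

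**The concern.** Late pain is a natural long-term outcome in a trial of two analgesic techniques. As the text stands, it would be analysed from the late score alone. Two things follow.

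First, precision. Patients differ in pain before surgery, and some of that difference is likely to persist. An unadjusted test leaves it in the error term. The sample size was set for the QoR-40 on day 3, so late pain has only the power that this number happens to give.

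Second, interpretation. The abstract's label suggests pain that followed the operation. Patient population excludes chronic opioid users, but it does not exclude patients with long-standing pain who take no opioids. Without a preoperative VAS, a high score at six months cannot be classed, on the same scale, as new, worse or unchanged.

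**Working it through.** **1. The plan's own figure (Sample size section).** Inputs: difference 6, SD 14, power 80%, alpha 0.05, taken as two-sided.

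n per arm = 2 × (1.960 + 0.842)² × (14/6)² = 2 × 7.849 × 5.444 = 85.5, rounded up to 86. The total is 172, and 172/0.90 = 191.1, rounded up to 192. The stated 86, 172 and 192 are reproduced. They concern the QoR-40 and are not affected by this point.

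**2. What the same number gives for late VAS.** The article states no SD, target difference or baseline correlation for VAS, so the result is in SD units. With 86 per arm and an unadjusted comparison of means:

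detectable difference = (1.960 + 0.842) × √(2/86) = 2.802 × 0.1525 = 0.427 SD.

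**3. Effect of adjusting for a preoperative score.** If that score correlates r with the late VAS, residual variance is multiplied by 1 − r² and the detectable difference by √(1 − r²). The values of r are assumptions.

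| r | residual variance (1 − r²) | detectable difference (SD) | unadjusted n per arm with equal precision, 86/(1 − r²) |
|---|---|---|---|
| 0 | 1.00 | 0.427 | 86 |
| 0.2 | 0.96 | 0.419 | 89.6 |
| 0.3 | 0.91 | 0.408 | 94.5 |
| 0.5 | 0.75 | 0.370 | 114.7 |
| 0.6 | 0.64 | 0.342 | 134.4 |

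For r from 0.3 to 0.5, variance falls by 9% to 25%. The detectable difference falls by 1 − √0.91 = 5% to 1 − √0.75 = 13%. These relative gains do not depend on how many patients still have a VAS at six months; the absolute SD figures do. The formula is for a comparison of means and does not carry over exactly to Mann-Whitney.

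**4. Is a preoperative VAS really absent?** Data collection schedules the QoR-40 only for postoperative days 1, 2 and 3, yet Statistical analyses uses a preoperative QoR-40. The collection text is therefore not exhaustive. The timeline of study procedures (Fig. 2) is not shown. The safe statement is that the text names no preoperative VAS.

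**The case against.** The strongest case against is that this is one of many secondary outcomes, that allocation is 1:1 and stratified by center, and that pre-existing pain is therefore balanced in expectation. The trial compares two techniques; it does not estimate how much pain surgery causes. Preoperative pain information is also already planned if the QLQ-C30 pain items are counted. Much of this stands. It rules out bias from the missing baseline and limits the point to precision and interpretation. It does not explain why the stated test should leave preoperative pain information unused. A further objection is that late VAS may be skewed, with many low scores, so that a linear model fits poorly. Residual checks, already planned for the primary outcome, and a rank test as a sensitivity analysis would meet this.

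The text does not support several stronger readings:

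- **Unblinded staff take the score.** A reader might infer this from the outpatient setting and from "Health care providers will also not be blinded". The text names neither the collector nor the mode. A patient may mark the scale and staff only register it.
- **No preoperative VAS exists.** This is firmer than a non-exhaustive schedule and a missing figure allow.
- **Late VAS should move to the questionnaires sent to patients, with the clinic score as fallback.** Patients know their allocation too ("which is considered unethical, patients will not be blinded"), so their own expectations would remain. A fallback would also mix modes within one outcome, depending on who responds.
- **A given share of chronic-pain cases predates surgery.** The article gives no VAS cut-off and no prevalence of pain before or after surgery, so no such share can be derived.

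**Conclusion.** The point holds as a modest, inexpensive improvement to a secondary outcome. It is not an error that threatens the trial. The primary outcome and sample size are untouched, and the randomized comparison of late pain is valid as planned.

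The loss is 9% to 25% of residual variance, or a detectable difference of 0.43 SD where 0.41 to 0.37 SD was available. This assumes a baseline correlation of 0.3 to 0.5 and 86 patients per arm with a late VAS. At r = 0.2 the gain is slight, at 4% of variance. The interpretive limit does not depend on r: without a preoperative VAS, pain that was already there cannot be separated on the same scale from pain at six months. If the full protocol already schedules a preoperative VAS, only the choice of analysis remains to be changed.

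**What to change.** 1. Check whether the full protocol or the timeline already includes a preoperative VAS, and say so in the text. If not, add one VAS line to the questionnaires already sent before surgery. It is best completed before the patient learns the allocation.
2. Replace the unadjusted test for the 3- and 6-month VAS with a linear model containing treatment, preoperative pain and center. Center is the stratification factor.
3. For patients already operated on, use the pain items of the preoperative QLQ-C30 as the baseline. The article does not list the contents of that questionnaire, so confirm that the items are held. Let the model have a separate intercept and slope for each type of baseline measure.

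The cost is one questionnaire line, a small amendment, and a different baseline measure for early patients. The article gives a start date of 3 December 2019 but not the number already operated on, so the size of that early group is unknown. The method of collecting the late VAS need not change.
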